**ABSTRACT**

**Rationale:** Change of practice environment and an interdisciplinary team is needed to implement evidence-based diabetes care which requires risk stratification, periodic assessments, education and treatment to targets.

**Hypothesis:** The use of a web-based disease management program (Joint Asia Diabetes Evaluation (JADE) Program) delivered by a doctor-nurse-HCA team reduces the incidence of all diabetes-associated clinical endpoint and improves control of risk factors compared to usual care (DIAbetes MONItoring Database (DIAMOND) group) in type 2 diabetes.

**Objective:** To compare structured care using the JADE portal versus usual care using the DIAMOND portal on incidence of all-diabetes related events, physical and psychological health.

**Study design:** A multicentre, randomized, integrated disease management program

**Setting and patients:** 600 patients from each site will be randomized to the JADE group (n=300) or the DIAMOND group (n=300) and followed up for at least 24 months.

**Intervention:** All patients will undergo comprehensive assessment (CA) guided by the templates in the respective portal at baseline, month 12 and 24. The JADE group will be further managed by a doctor-nurse-HCA team guided by the JADE portal with risk stratification program and recommendation to different care protocols with predefined follow up (FU) schedules, information sharing and decision supports.

**Outcome measures:** Primary composite outcomes include all diabetes-related clinical events; secondary composite outcomes include control of risk factors and tertiary composite outcomes include behavioral changes, psychological health, quality of life and cost-effective analysis.

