#### Manpower estimation

From each participating centre, 600 consecutive type 2 diabetic patients will be recruited. Each day, approximately 4-6 patients can undergo CA performed by the doctor-nurse-HCA team. We expect to complete recruitment in 6-8 months with 300 patients randomized to the usual care (DIAMOND) and 300, to structured care (JADE) (see example for suggestion of workflow).

|           | Mon                          | Tues                                      | Wed                          | Thurs                                     | Fri                          |
|-----------|-------------------------------------|--------------------------------------------------|-------------------------------------|--------------------------------------------------|-------------------------------------|
| AM | CA
of 4-6 patients               | CA
of 4-6 patients                            | CA
of 4-6 patients               | CA
of 4-6 patients                            | CA
of 4-6 patients               |
| PM | Data entry
Reminder
Education | FU clinic of 10
JADE patients by
trio-team | Data entry
Reminder
Education | FU clinic of 10
JADE patients by
trio-team | Data entry
Reminder
Education |

Assuming 4 patients daily and 20 patients weekly, 600 patients will be enrolled in 30 weeks. On average, each patient has 4 team-based visits yearly to give 1200 patient-visits. Assuming 10 patients per session, this will give 120 clinic sessions, i.e. 2 clinics weekly. The nurse-HCA will use other sessions to educate patients, manage data, recall default, check protocol adherence and risk factor control, as guided by the doctor.

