#### Complications and risk factors in 3687 Asian T2D patients

[figure not shown]

So WY et al for JADE Study Group J of Diabetes 2011

We used these observations to estimate the sample size needed to give a 2-year study 80% power with an alpha value of 0.05 to confirm the superiority of team-based structured care over usual care on clinical endpoints. We used different combinations of scenarios including an annual hazard rate ranging from 0.01 to 0.10 in the usual care group and a HR ranging from 0.5 to 0.85 in the structured care group with an attrition rate of 0.2, to estimate the sample size. Using the most conservative scenario where the annual hazard rate is 0.02, i.e. 0.04 in 2 years and assuming a HR of 0.8 in the structured care group, the study will have sufficient power to confirm the primary hypothesis. For high risk patients with a hazard rate of 0.05 and those with medium risk (0.03), and assuming a modest HR of 0.8 in the structured care group, a sample size of 6626-13762 patients will give the study 80% power at an alpha value of 0.05.

|                                                     |      |       |                |      |       |       |
|-----------------------------------------------------|------|-------|----------------|------|-------|-------|
| 80% power at 0.05 alpha
minimum 2 year follow up |      |       |                |      |       |       |
| LOW RISK                                            |      |       | VERY LOW RISK  |      |       |       |
| hazard ratio                                        | 0.5  | 0.8   | 0.85           | 0.5  | 0.8   | 0.85  |
| annaul hazard rate                                  | 0.02 | 0.02  | 0.02           | 0.01 | 0.01  | 0.01  |
| hazard rate (usual)                                 | 0.04 | 0.04  | 0.04           | 0.02 | 0.02  | 0.02  |
| hazard rate (structured)                            | 0.02 | 0.032 | 0.034          | 0.01 | 0.016 | 0.017 |
| absolute difference                                 | 0.02 | 0.008 | 0.006          | 0.01 | 0.004 | 0.003 |
| sanple size in each group                           | 1239 | 8760  | 15868          | 2515 | 17838 | 32333 |
| total sample size                                   | 2478 | 17520 | 31736          | 5030 | 35676 | 64666 |
| assuming 20% attrition rate                         | 2974 | 21024 | 38083          | 6036 | 42811 | 77599 |

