#### Validation of risk equations derived from the Hong Kong Diabetes Registry

Assuming a 2% annual incidence of all diabetes-related event rates including death, stroke, heart disease, lower extremity amputation, visual impairment, renal failure and cancer, i.e. 4% in 2 years, a sample size of 596 will confirm this estimate with an error of 1% for each

participating centre. In our previous analysis, we have shown that the UKPDS risk engine under-estimated the stroke rate and, over-estimated the CHD rates in Chinese type 2 diabetic patients. Furthermore, compared to our risk equations, UKPDS does not utilize important risk parameters such as eGFR, ACR and blood hemoglobin which are powerful predictors of clinical endpoints in Asian populations (41) (42).

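### The risk-equation validation is sized on 596 patients per centre, which mixes both arms, makes no allowance for attrition, and does not give the stated 1% error

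*Protocol*

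**What the plan says.** The protocol's sample size chapter ends with a section headed Validation of risk equations derived from the Hong Kong Diabetes Registry. It begins "Assuming a 2% annual incidence of all diabetes-related event rates", converts this to 4% over two years, and states that "a sample size of 596 will confirm this estimate with an error of 1% for each" participating centre. It gives no confidence level and mentions neither study group nor attrition.

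Three other statements bear on it:

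- **Centre size and allocation.** The Abstract says "600 patients from each site will be randomized to the JADE group (n=300) or the DIAMOND group (n=300"). Manpower estimation repeats the split: "300 patients randomized to the usual care (DIAMOND) and 300, to structured care (JADE").
- **Expected effect of JADE.** Under Primary composite outcome the sizing considers "a HR ranging from 0.5 to 0.85 in the structured care group", with its conservative scenario "assuming a HR of 0.8 in the structured care group". The low-risk block of that table gives a 4% two-year rate to usual care and, at a hazard ratio of 0.8, 3.2% to structured care.
- **Attrition.** The same text uses "an attrition rate of 0.2", and the sample size tables for the primary and secondary outcomes each carry a row for it.

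Nothing in the protocol restricts the validation to one arm. Data Analysis names intervention group as a covariate only in a logistic regression for predictors of the primary endpoint, which is not described as a validation of the equations.

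**The concern.** A calibration check compares the number of events observed with the number the equations predict. In half of each centre's patients, the programme under test is expected to reduce those events. JADE follow-up also depends on risk level, and the risk scores help to define that level, so in that arm the prediction influences the care received. A single rate over both arms therefore describes neither kind of care if the trial's own hypothesis is right.

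The protocol also uses the same 4% in two incompatible ways: as the usual-care rate in the low-risk block of the primary sizing, and as the whole-centre rate here.

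Separately, the sentence promises a precision. If 596 does not deliver it, each centre is told that it can confirm an event rate more closely than it can. At stake is how a secondary use of the data is read. The randomised comparison of JADE with DIAMOND is not affected.

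**Working it through.** **Inputs (all from the protocol).** Two-year rate p = 0.04, error d = 0.01 and n = 596 (validation section); 600 per centre, 300 per arm (Abstract, Manpower estimation); hazard ratio 0.8, range 0.5 to 0.85, and attrition 0.2 (Primary composite outcome). The confidence level is not stated. I use 95%, in line with the two-tailed 0.05 in Data Analysis.

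**1. Reproducing 596.** For one proportion, n = z²p(1−p)/d².

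- 95%: 1.96² × 0.04 × 0.96 / 0.01² = 1,475.1, so 1,476
- 90%: 1,039
- 80%: 631
- 1% read as a standard error: 0.0384 / 0.0001 = 384
- p = 0.02 in place of 0.04: 753 at 95%, 531 at 90%

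None of these is 596, and multiplying by 1.2 or dividing by 0.8 for attrition does not produce it. The one precision calculation that does is p = 0.04 at 95% with a finite-population correction for N = 1,000: 1475.1 / (1 + 1475.1/1000) = 596.0. The protocol mentions no population of 1,000.

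**2. Precision actually available.** The 95% half-width is 1.96 × √(0.04 × 0.96 / n).

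| Patients | n | Half-width (points) |
|---|---|---|
| Stated number | 596 | 1.57 |
| Whole centre after 20% loss (600 × 0.8) | 480 | 1.75 |
| DIAMOND, no loss | 300 | 2.22 |
| DIAMOND after 20% loss (300 × 0.8) | 240 | 2.48 |
| Needed for 1 point | 1,476 | 1.00 |

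With 596 patients, ±1 point corresponds to about 79% confidence (0.01 / 0.00803 = 1.246 standard errors). The protocol's tables allow for attrition by multiplying by 1.2 (2,478 becomes 2,974). Read that way, a centre of 600 has 600/1.2 = 500 evaluable, half-width 1.72, which changes little.

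**3. Effect of mixing the arms.** Suppose the equations correctly predict 4% under usual care, and apply the hazard ratio to the two-year rate as the protocol's table does. The combined rate is p_c = (0.04 + 0.04 × HR)/2. The chance that one centre's 95% interval lies wholly below the correct 4% is Φ((0.04 − p_c)/SE − 1.96), with SE = √(p_c(1−p_c)/596).

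| HR | JADE rate | Combined rate | Observed/expected | Shift (points) | Chance, n = 596 |
|---|---|---|---|---|---|
| 0.85 | 3.4% | 3.7% | 0.925 | 0.3 | 6% |
| 0.8 | 3.2% | 3.6% | 0.90 | 0.4 | 8% |
| 0.5 | 2.0% | 3.0% | 0.75 | 1.0 | 30% |

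For HR 0.8: SE = √(0.036 × 0.964/596) = 0.00763, and 0.004/0.00763 − 1.96 = −1.44, giving 0.08. The nominal value is 2.5%. Per 600 patients this is 21.6 events observed against 24 expected.

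**4. Pooling centres.** Sampling error falls as centres are added, but the shift does not. At HR 0.8 the 0.4-point shift equals the 95% half-width at n = 1.96² × 0.036 × 0.964 / 0.004² ≈ 8,330 evaluable patients from both arms. In DIAMOND alone, ±1 point is reached at about 1,476 patients: 5 centres with 300 evaluable each (1,476/300 = 4.9), or 7 with 240 (1,476/240 = 6.2).

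**The case against.** The strongest reply is that the section plans precision per centre, and at that level the shift hardly matters. At HR 0.8 it is 0.4 point, less than even the stated 1-point error, and the chance of wrongly excluding 4% rises only from 2.5% to about 8%. Within a centre, using both arms can even give the smaller total error. With 480 evaluable patients at HR 0.8 the root-mean-square error is √(0.85² + 0.40²) = 0.94 point, against a standard error of 1.26 for 240 DIAMOND patients. At HR 0.5 the two are about equal (1.27 and 1.26). This stands. It limits the size of the problem in one centre, but it does not make the combined rate the right quantity, and it gives no help once centres are pooled.

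Three stronger readings are tempting, and the protocol does not support them:

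- **That only about 240 patients per centre can inform the validation.** JADE patients can inform discrimination, and calibration too if allocation is modelled. The figure of 240 also assumes that attrition removes outcome data, whereas Default and Missing Data plans contact about clinical status at least yearly, even for patients who do not return. Before attrition the number is 300.
- **That DIAMOND alone gives an unbiased check.** The protocol does not say what care registry patients received. DIAMOND patients have comprehensive assessments at baseline, 12 and 24 months, and in the one-year pilot risk factors improved in both groups. Observed events could therefore fall below prediction in DIAMOND as well.
- **That the equations would then be recalibrated downwards.** The protocol plans no recalibration and no change of risk levels, and validation is not among its listed objectives.

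It might also be said that the analysis plan will settle the matter. It can settle the method, but the protocol itself fixes a number and a precision, and both are in question.

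**Conclusion.** The point holds as a defect in a stated sample-size justification. The 596 per centre needs both arms of a 600-patient centre and leaves 4 patients for attrition. The single 4% rate conflicts with the protocol's own assumption that JADE lowers event rates. The stated precision is not delivered either: at 95% it is about ±1.6 points with 596 patients and ±1.75 with 480, and ±1 point needs about 1,476.

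The precision result needs only the stated 4% rate and a 95% level. The size and direction of the calibration shift (observed/expected 0.90 at HR 0.8, 0.75 to 0.925 over the protocol's range) rest on three assumptions: that the equations predict usual-care risk, that the planning hazard ratio applies to the events listed in the validation section, and that JADE works as planned. In one centre the shift at HR 0.8 would rarely be noticed; pooled over many centres it would remain. If the first assumption fails, the direction is open, but a rate averaged over two arms expected to differ is still not a clean test. The primary comparison is untouched.

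**What to change.** In the validation section:

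1. State that calibration is assessed by arm, either with DIAMOND as the main estimate or with both arms and allocation in the model. Report observed/expected in JADE separately, as a description of risk under the programme.
2. Make the estimate pooled across centres the main one.
3. Replace the 596 and its 1% error with the evaluable number after attrition and its 95% precision at a 4% rate: about ±2.2 points with 300 DIAMOND patients in a centre, ±2.5 with 240, and below ±1 point once at least about 1,476 DIAMOND patients are pooled.
4. State the confidence level and, if a finite-population correction lies behind 596, the population and the reason for it.
5. Say what care the equations' predictions are taken to represent, so that the comparison has a defined target.

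This is a change of wording and of analysis set, with no new data. The cost is that calibration within a centre is less precise than the protocol now says, and the per-centre 1% claim has to go.

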## **DATA ANALYSIS**

All data will be analyzed using the SPSS statistical software (Windows 13.0 version, Chicago, USA). A p value of 0.05 or less (2-tailed) will be considered significant. For the primary composite endpoint, an intention to treat analysis will be performed including all patients randomized to both groups who have at least returned for one visit or contacted by phone once post randomization to ascertain clinical status (alive, dead or hospitalized). Descriptive analysis will be used to report all clinical and laboratory parameters. Student's t-test, Chi-squared test and Analysis of Co-variance will be used for between-group and within-group comparisons for all baseline data and endpoints, as appropriate. Kaplan-Meier curve analysis will be used to compare the incidence of primary composite endpoint between the JADE and DIAMOND group adjusted for age, sex, ethnicity and disease duration. Interaction between group assignment and covariates including age, gender, duration of diabetes (< or ≥8 years), socioeconomic group, complications, risk factors, JADE risk categories, compliance and psychological health parameters will be examined. Logistic regression will be used to determine independent predictors for achieving primary composite endpoint using all relevant covariates including age, gender, duration of diabetes (< or ≥8 years), centre characteristics, socioeconomic group, risk levels, metabolic and risk factor control, compliance, self care, psychological health parameters and intervention groups.

A per protocol analysis will be performed in the JADE group with details of intervention, where we shall compare baseline clinical profile, care processes, number of visits and use of medications between patients who develop and those who do not develop clinical endpoints. A sensitivity analysis will also be performed using hazard rates of the JADE and DIAMOND group amongst those who have defaulted.

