#### Objectives and expected outcomes of AP -JD Program

In this demonstration project (Asia Pacific JADE and DIAMOND Program, AP-JD in short) supported by ADF, patients will be recruited from different sites across Asia, with each site recruiting at least 600 type 2 diabetic patients. After explanation by trained doctors and nurses, and with written informed consent, patients will be randomized to either the JADE (n=300, structured care) or DIAMOND (n=300, usual care) group. All patients will undergo a comprehensive assessment (CA) at baseline and yearly thereafter. Patients in the JADE group will be further managed by a doctor-nurse-HCA team according to a protocol based on risk stratification with predefined follow up (FU) schedules together with shared information and decision support (i.e. structured collaborative care). The DIAMOND protocol involves only baseline and yearly CA without predefined FU schedules or feedback of information between CA visits (i.e. usual care). The primary composite endpoint is all-diabetes related clinical endpoints. The secondary composite endpoint is attainment of treatment goals and/or control of risk factors. The tertiary changes are behavioral changes, psychological well being and quality of life.

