## **SETTING AND PATIENTS**

In this program, 600 consecutive type 2 diabetic patients will be recruited from each participating centre during a 6-8 month period, with randomization to either the JADE or DIAMOND group in a 1:1 ratio.

*Inclusion criteria*

- 1) Type 2 diabetic patients who are willing or can be persuaded to return for 'regular' follow-up at 3-4 monthly intervals
- 2) Aged  $\geq 18$  years
- 3) Patients with newly diagnosed or established disease, treated with lifestyle modification or blood glucose lowering drugs including oral agents with or without insulin
- 4) For newly diagnosed type 2 diabetic patients, their plasma glucose levels should be:
  - a) Fasting plasma glucose (PG)  $\geq 7.0$  mmol/L on 2 or more occasions, and/or
  - b) Random or 2-hour PG  $\geq 11.1$  mmol/L (after 75 gram oral glucose tolerance test) on 2 or more occasions, and/or
  - c) HbA1c  $\geq 6.5\%$

*Exclusion criteria*

- 1) Type 1 diabetes defined as a history of ketosis at diagnosis [acute symptoms with heavy ketonuria ( $>3+$ ) or ketoacidosis] or continuous requirement of insulin within one year of diagnosis (38).
- 2) Patients with reduced life expectancy (e.g. less than 6 months) due to recent diagnosis of advanced cancers (e.g. within last 2 years) and other life-threatening conditions.
- 3) Patients with a mental condition rendering them unable to understand the nature, scope, and possible consequences of the study.
- 4) Patients actively enrolled in another intervention study.
- 5) Patients who are unwilling to return for regular follow up.

**OUTCOME MEASURES***Composite primary endpoint (CRF (1-5))*

- 1) Incidence of all diabetes-related endpoints including:
  - a) cardiovascular events (acute myocardial infarction, revascularisation procedures, heart failure, unstable angina, arrhythmia, stroke, transient ischemic attacks requiring hospital admissions) and related death
  - b) chronic kidney disease (eGFR  $< 60$  ml/min/1.73m^2) or end stage renal disease (dialysis and/or eGFR  $< 15$  ml/min/1.73m^2) and related death
  - c) visual impairment (corrected visual acuity of 20/200 or worse) or eye surgery (cataract removal, retinal surgery and vitrectomy)

- d) lower extremity amputation or foot ulcers requiring hospitalizations
- e) major infections – pulmonary and non-pulmonary requiring hospitalizations
- f) all-site cancers
- g) death

Composite secondary endpoint

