### Randomization

Computer-generated codes numbered 1 to 600 with assignment to either JADE or DIAMOND group will be prepared by ADF for each site. Three sets of envelopes with equal assignment to JADE or DIAMOND Group will be given to the study site at regular time intervals depending on rate of recruitment. The randomization procedures are as follows:

- 1) The doctor or nurse will explain to eligible patients regarding the international recommendation on performing regular CA to detect silent risk factors and complications.
- 2) They will also explain to patients the need to assess cost-effectiveness of using a team to implement structured care by comparing the latter with usual care.
- 3) After the patient has signed the consent, a staff not participating in the study will open the envelope containing the randomization group and sign and date the envelope.
- 4) The signed envelope will be kept by the nurse in a secure place for audit purpose.
- 5) The nurse will explain to patient whether they have been randomized to JADE or DIAMOND and the assessment will proceed accordingly.
- 6) The nurse will fax the randomization form to the ADF office and keep a log of randomized patients and record status including study completion, premature discontinuation, consent withdrawal or lost to follow up.
- 7) The doctor or nurse will contact the ADF to obtain the user code to enrol the patient in either the JADE or DIAMOND portal and obtain a patient identification number (ID).

[figure not shown]

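### The primary comparison is called an adjusted Kaplan-Meier analysis, with no model, test or effect measure named and site left out; the separate logistic predictor model should not be read in its place

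*Protocol*

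**What the plan says.** The protocol's Data Analysis section gives the primary comparison in one sentence: "Kaplan-Meier curve analysis will be used to compare the incidence of primary composite endpoint between the JADE and DIAMOND group adjusted for age". The full list of covariates is "adjusted for age, sex, ethnicity and disease duration". No log-rank test, Cox model, weighting scheme or hazard ratio is named for it. The same section allows a t-test, chi-squared test or analysis of covariance for endpoints, as suits.

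A second analysis follows: "Logistic regression will be used to determine independent predictors for achieving primary composite endpoint using all relevant covariates". Its covariates include "centre characteristics, socioeconomic group, risk levels, metabolic and risk factor control, compliance, self care, psychological health parameters and intervention groups". No measurement time is given for any of them.

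On design, the executive summary states that "patients will be randomized to either the JADE (n=300, structured care) or DIAMOND (n=300, usual care) group", Setting and Patients repeats this "with randomization to either the JADE or DIAMOND group in a 1:1 ratio", and Randomization says "Computer-generated codes numbered 1 to 600 with assignment to either JADE or DIAMOND group will be prepared by ADF for each site". Individual patients are therefore randomised within site. Logistics and Timeline gives follow-up of at least 24 months, closing 3 years after the first patient enters. The sample size section assumes a hazard ratio of 0.8 and 20% attrition, and expects clinics, patients and health systems to differ between sites.

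**The concern.** The sentence that defines the primary result asks a method for something it does not do. Two analysts could follow it and report different primary p-values, for example from an unadjusted log-rank test, a Cox model, or Kaplan-Meier curves within age bands. Each would be consistent with the text. None of these options is tied to the site-specific randomisation lists.

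With the adjusted comparison undefined, the logistic model is the only named regression that is said to contain both the primary endpoint and the group term, so it may be read as the adjusted treatment effect. It is badly suited to that. It takes no account of time at risk. It may also condition on things the intervention is meant to change: the protocol's hypothesis is that JADE improves risk factor control, which is the secondary endpoint, and compliance and self-care behaviours are tertiary endpoints. A working intervention could then look weaker than it is.

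**Working it through.** **1. What the named method can do.** The Kaplan-Meier estimator is S(t) = ∏(1 − dᵢ/nᵢ), where dᵢ is the number of events and nᵢ the number at risk at each event time. It has no term for age or disease duration. Adjustment needs a regression, stratification or weighting, and the section names none of these.

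**2. The plan's own figure.** For 2-year risks of 0.04 and 0.032 (ratio 0.8), two-sided alpha 0.05 and 80% power, the two-proportion formula gives

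n = [1.96·√(2·0.036·0.964) + 0.8416·√(0.04·0.96 + 0.032·0.968)]² / 0.008² = 8,511 per group.

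With the continuity correction, n/4·[1 + √(1 + 4/(n·0.008))]² = 8,760. This is the protocol's figure exactly (17,520 in total).

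**3. Does a time-to-event analysis change the size?** By Schoenfeld's formula, events = 4·(1.96 + 0.8416)²/(ln 0.8)² = 4·7.849/0.0498 = 631. With a usual-care hazard of 0.02 per year over 2 years, the event probabilities are 1 − e^(−0.04) = 0.0392 and 1 − e^(−0.032) = 0.0315, with mean 0.0354. Patients needed: 631/0.0354, about 17,850, against 17,520 before attrition.

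**4. Leaving site out.** Assumption: site hazards are spread evenly from 0.01 to 0.10 per year. The protocol gives that range for usual-care scenarios, not for sites. The mean is 0.055 and the variance 0.09²/12 = 0.000675. The pooled cumulative hazard is approximately mean·t − variance·t²/2.
- At 2 years: usual care 0.1100 − 0.00135 = 0.10865; structured care, with all hazards multiplied by 0.8, 0.0880 − 0.00086 = 0.08714; ratio 0.802.
- At 2.7 years the ratio is 0.803.

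An illustrative simulation agrees. It assumed 20 sites of 600 patients, site standard deviation 0.7 on the log hazard, a usual-care hazard of about 0.05 per year, follow-up of 2 to 3 years, 20% attrition and an effect of about 0.80. The average hazard ratio was 0.812 without site and 0.808 stratified by site.

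**5. Conditioning on on-study risk factor control or compliance.** If a share m of the log hazard ratio acts through these variables, the group effect that remains is exp[(1 − m)·ln 0.80]. The documents do not give m.

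| Assumed m | Remaining effect |
|---|---|
| 0.5 | 0.894 |
| 0.8 | 0.956 |
| 1.0 | 1.00 |

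In the same simulation, risk factor control was assumed to be reached by 60% against 45% and to halve the hazard. The logistic odds ratio moved from 0.805 to 0.892 when control was added. On the log scale, 1 − ln 0.892/ln 0.805 = 1 − 0.114/0.217 = 47% of the effect was removed.

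**6. Ignoring follow-up time.** With equal attrition the harm was small: odds ratio 0.805 beside a stratified hazard ratio of 0.808. With assumed attrition of 10% in JADE and 30% in DIAMOND and a true hazard ratio of 0.80, Cox gave 0.802 and the logistic model 0.919. A rough check: if those who leave contribute 1 year on average and the others 2.5 years, mean exposure is 0.9·2.5 + 0.1·1 = 2.35 years against 0.7·2.5 + 0.3·1 = 2.05 years, and 0.80·2.35/2.05 = 0.917.

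**The case against.** The strongest reply is that this is a wording slip which an analysis plan would settle. Hazard ratios run through the sample size section, the Data Analysis section mentions hazard rates in a sensitivity analysis, and stratified or weighted forms of Kaplan-Meier exist. An unadjusted Kaplan-Meier or log-rank comparison of randomised arms is valid without any covariates. All of that stands, so a reader who infers that the trial could produce no valid treatment effect goes too far. But the point is not that detail is absent: the protocol states a method, and the method as named does not do what is asked of it.

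On the logistic model, the reply is also partly right. Its stated purpose is to find predictors, not to estimate the treatment effect, and it includes centre characteristics. The planned interaction tests also imply some other model with a group term, though its form is not given. HbA1c, blood pressure, lipids, compliance, self care and depression scores are all collected at the baseline assessment, so the covariates may be baseline values. A reader might infer that the group coefficient is pulled to the null by design. The text does not support that; it happens only if on-study values are used. That use is permitted by the wording and plausible, since improved control is partly defined as a reduction from baseline and JADE compliance is checked at each follow-up visit.

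A reader might also take site to be the unit of randomisation and see a clustering error. Patients are randomised individually from a list for each site, so site is a stratum. Nor is the hypothesis stated as a hazard ratio: it speaks of incidence and event rates. Only the sample size assumptions use one.

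**Conclusion.** The point holds in this form. The adjusted primary comparison cannot be run as described, because no model, test or effect measure goes with the covariates, and it leaves out the stratum used in randomisation. This bears on the primary result and should be settled before any comparison by group.

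The parts differ in size. The undefined comparison is a matter of definition and has no single number. Leaving site out changes a true 0.80 by about 0.01 or less in the cases examined; the case for including it is efficiency and agreement with the randomisation, not bias.

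The risk from the logistic model is conditional. Its group coefficient would move from 0.80 to about 0.89 if on-study values are used and half of the effect is mediated. It would move to about 0.92 if attrition were 10% against 30%. Neither the mediated share nor attrition by arm is given in the protocol, so these are illustrations. Unequal loss is plausible, because JADE patients are reviewed every 2 to 4 months and DIAMOND patients have scheduled assessments only at 12 and 24 months.

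**What to change.** Replace the Kaplan-Meier sentence with:

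> Time from randomisation to first primary event will be compared by a Cox model stratified by site, with baseline age, sex, ethnicity and disease duration as covariates, giving HR and 95% CI; Kaplan-Meier curves and a site-stratified log-rank test are supportive.

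This keeps all four covariates that the protocol already lists.

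For the logistic predictor model, state when each covariate is measured. Either use baseline values, or label the model descriptive and add that its group coefficient is not to be interpreted as the treatment effect when on-study values are included.

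The cost is one paragraph of wording. No extra data are needed: sites have their own lists, envelopes are dated when opened, and event dates are needed for any Kaplan-Meier curve. The number of patients hardly changes.
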